### Interim analyses {21b}

An interim analysis will be performed when the trial completes the follow-up of 30 patients to assess for safety and outcomes. The trial will be terminated in case of significant harm or if significant statistical difference on the primary outcome is achieved.

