### Sample size {14}

The sample size was calculated using the statistical noncentral *t *function, with a one-sided alpha level of 0.05 [31]. The calculations were based on the expected renal function and IAP variation between groups, since we assume the former to be dependent of the latter.

To support the trial rationale of an expected clinically significant IAP decrease of 3 mmHg in the intervention group, a total of 44 patients are considered necessary to detect a statistically significant difference, with 1:1 allocation ratio, 80% statistical power, and 95% confidence level. This estimate is based in a post-hoc analysis of 61 patients with cirrhosis from a multicentric randomized controlled trial in shock patients where a mean difference in IAP of 3 mmHg was found between survivors and non-survivors (13.7 ± 3.9 and 16.7 ± 3.9 mmHg, respectively) [4].

Regarding the primary outcome, to detect a clinically and statistically significant decrease in serum creatinine of 0,4 mg/dL in the intervention group, a total of 60 patients is estimated, with a 1:1 allocation ratio, 95% statistical power, and 95% confidence. This estimate is based on a multicentric observational study of acutely decompensated patients with cirrhosis. In this study, cirrhotic acute-on-chronic liver failure patients with at least one organ failure had a mean creatinine difference of 0,4 mg/dL between survivors and non-survivor groups (0.9 ± 0.45 and 1.3 ± 0.48 mg/dL) [32].

We arbitrarily estimate that protocol non-adherence/attrition or violation after randomization may affect approximately 15% of cases and, therefore, to ensure that the number of patients that complete the protocol is reached for the primary outcome, the total sample size is set at 70 patients with a 1:1 group allocation ratio.

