## Statistical methods

### Statistical methods for primary and secondary outcomes {20a}

For the descriptive analysis, quantitative variables will be reported as means and standard deviations or as medians and interquartile ranges (*P*_25_-*P*_75_), as appropriate, and categorical variables reported as frequencies and percentages.

Quantitative variables will be analyzed using the assessment day value (D7), the daily mean value, and their maximum or minimum values. Mann–Whitney *U* test will be used to compare study groups, assuming a non-normal distribution, or two independent sample *t*-test, in case of normal distribution. Dichotomous categorical variables will be analyzed using chi-square or Fisher’s exact tests. Using daily values, mixed effects regression models will be used to consider the autocorrelation structure between the longitudinal measurements. Regarding stage 3 AKI as secondary outcome, odds ratios and corresponding 95% confidence intervals will be estimated using logistic regression models. For the study of RRT-free days, competing risks survival models will be applied considering death as the competing risk. Regarding time until death, joint survival regression models will be used to take into consideration the association of longitudinal markers with time until death. For LOS, linear regression models will be applied. For all regression studies, univariable and multivariable analyses will be performed to account for potential confounders. The absolute risk of paracentesis-related complications will be reported for both trial groups. A level of significance *α*= 0.05 will be considered. Data will be analyzed using the R Statistical Software [41].

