### Composition of the data monitoring committee, its role and reporting structure {21a}

A data monitoring committee (DMC) composed of three independent external collaborators, including a statistician, will report to the PI and the Research Center on aspects of trial conduct, such as recruitment, identify the need to make adjustments, and analyze for significant outcomes or harm.

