### Frequency and plans for auditing trial conduct {23}

The DMC is expected to perform  trial conduct audits once 20 and 40 randomized patients have completed 28-day follow-up and at trial conclusion.

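### The interim stopping rule for efficacy at 30 patients names no adjusted level; applying 0.05 there and again at the end gives an overall type I error of about 8.5%, not 5%

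*Protocol article*

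**What the plan says.** The section Interim analyses {21b} of the protocol article fixes the timing and purpose of the look: "An interim analysis will be performed when the trial completes the follow-up of 30 patients to assess for safety and outcomes". It then gives the decision rule: "The trial will be terminated in case of significant harm or if significant statistical difference on the primary outcome is achieved". No boundary, spending function or reduced level appears there, and the section points to no other document for one.

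Statistical methods for primary and secondary outcomes {20a} gives the only analysis level: "A level of significance *α*= 0.05 will be considered". It states neither the sidedness nor whether the level applies to each look or to the trial as a whole. Sample size {14} was calculated "with a one-sided alpha level of 0.05", with no allowance for an interim look.

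Two sections describe the data monitoring committee. Section {21a} includes in its remit to "analyze for significant outcomes or harm", without saying when. Section {23} schedules audits of trial conduct once 20 and 40 "randomized patients have completed 28-day follow-up", and again at the end, with no test or stopping rule attached.

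**The concern.** Section {21b} is more than an announcement that the data will be looked at. It sets the time, the endpoint, the criterion (statistical significance) and the consequence (termination). Read with the single level of 0.05 in {20a}, it gives the trial two chances to declare a difference at the nominal level, and the chance of a false positive then exceeds 5%.

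There is a second cost. With about 15 patients per arm, only a large observed difference reaches significance, so a trial that stops early tends to report too large an effect. It also stops with less than half the planned information on secondary outcomes and catheter complications. The Discussion already concedes that the full sample may be too small for some of these, so early stopping worsens that limitation but does not create it.

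**Working it through.** **Inputs.** Interim at 30 patients ({21b}); final sample 70, with 60 required ({14}); level 0.05 ({20a}); one-sided 0.05 for planning ({14}); planning difference 0.4 mg/dL from groups with "0.9 ± 0.45 and 1.3 ± 0.48 mg/dL" ({14}). Pooled SD = √[(0.45² + 0.48²)/2] = 0.465.

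**The plan's own figure.** The noncentral t calculation with difference 0.4, SD 0.465, one-sided 0.05 and 95% power gives 30 per arm, 60 in total (power 95.0%), as stated. A two-sided test would need 74. The whole one-sided 0.05 is therefore spent on one final test.

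**Overall type I error with 0.05 at both looks.** Under no difference, the interim and final statistics are approximately bivariate normal with correlation √(n₁/n₂). The overall error is 1 − P(no crossing at either look) = 2 × 0.05 − P(crossing at both).

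| Looks | Correlation | Two-sided (1.960) | One-sided (1.645) |
|---|---|---|---|
| 30, 70 | √(30/70) = 0.655 | 0.100 − 0.0146 = 8.5% | 0.100 − 0.0176 = 8.2% |
| 30, 60 | √(30/60) = 0.707 | 0.100 − 0.0169 = 8.3% | 0.100 − 0.0199 = 8.0% |

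Simulated two-sided t-tests at 30 and 70 (100,000 runs) give 8.6%. With the Mann–Whitney test, the other option in {20a}, simulation gives 7.8%. These error rates do not depend on the planning SD.

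**Size of effect on early stopping (two-sided 0.05, 15 per arm).**
- Standard error = 0.465 × √(2/15) = 0.170. The critical t on 28 degrees of freedom is 2.048, so the observed difference must exceed about 2.048 × 0.170 = 0.35 mg/dL.
- At the planning difference of 0.4, the noncentrality is 0.4/0.170 = 2.35. About 62% of trials stop, with a mean estimate of 0.50, which is 0.50/0.40 = 1.25 times the truth.
- At 0.2 mg/dL, an assumption not found in the document, about 20% stop, with a mean estimate of about 0.42.

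**Boundaries that hold the level.** The Lan-DeMets O'Brien-Fleming-type function spends, per side with level a, 2[1 − Φ(z₁₋ₐ⸝₂/√t)] at information fraction t = 30/70 = 0.43.
- Two-sided 0.05 (a = 0.025): 2[1 − Φ(2.241/0.655)] = 0.00062 per side, so p<0.0012 at the interim and p<0.0496 at the end.
- One-sided 0.05 (a = 0.05): 2[1 − Φ(1.960/0.655)] = 0.0028, so p<0.0028 at the interim and p<0.0491 at the end.
- Haybittle-Peto, two-sided: p<0.001 at the interim, then 0.05 at the end gives 5.03% overall; p<0.0497 at the end gives 5%.

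With 30 per arm and a one-sided final test at 0.0491 in place of 0.05, power of the final test moves from 95.0% to 94.9%.

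**The case against.** The strongest reply is that 0.05 in {20a} may be the overall level. The article condenses a longer protocol, and a numerical boundary often sits in an analysis plan or committee charter. The monitoring committee also includes a statistician. This stands to the extent that the 8.5% is conditional: it holds if 0.05 is used at both looks. It does not remove the point. The article does not simply leave the boundary out; it states a full rule with significance as the criterion, and the only level in the document is 0.05. If a boundary exists elsewhere, {21b} as worded needs to be brought into line with it.

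Two stronger readings are tempting, and the document does not support them.

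- A reader might infer that the error reaches about 12%, by counting the committee's reviews at 20 and 40 patients as further efficacy looks. Four two-sided tests at 20, 30, 40 and 70 would give 12.3%. But {23} presents those reviews as audits of conduct with no test or stopping rule, and {21a} gives no timing for analysing outcomes. Nor does a different audit schedule contradict the interim at 30. This is an ambiguity to clear up.
- A reader might infer that an early stop would double the effect. That follows only from the assumed 0.2 mg/dL. At the plan's own 0.4 the exaggeration is about 1.25-fold.

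It is also fair to object that the SD of 0.465 comes from the cited cohort and takes no account of the 4 mg/dL assigned for renal replacement therapy or death in Outcomes {12}. The stopping probabilities and mean estimates are therefore illustrations, not forecasts. The type I error figures are unaffected.

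**Conclusion.** The point holds. As worded, the efficacy rule in {21b}, combined with the single level in {20a}, does not keep the stated 5%. The overall error is about 8.5% two-sided or 8.2% one-sided with a final analysis at 70, and 8.3% or 8.0% at 60. The result hardly depends on sidedness or attrition. It assumes that 0.05 is applied at both looks and that no boundary is set in a document not shown. The overstatement of the effect on early stopping is real but depends on the true difference and on the planning SD. The 12% figure would apply only if the audits at 20 and 40 patients were also tests of the primary outcome at 0.05 that could end the trial, which the text does not say.

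**What to change.** In Interim analyses {21b}, replace the efficacy criterion with a named boundary, and first state whether the final test is one- or two-sided, since {14} plans one-sided and {20a} is silent.

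- Two-sided 0.05: O'Brien-Fleming-type spending, p<0.0012 at 30/70 and p<0.0496 at the end.
- One-sided 0.05: about p<0.0028 and p<0.0491.
- Haybittle-Peto, p<0.001 at the interim, is a simple alternative.

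Naming the spending function allows the levels to be recalculated if the actual information fraction is not 30/70. Put the final level in {20a} as well. The harm criterion need not change. In {21a} or {23}, add a sentence that the audits at 20 and 40 patients involve no efficacy test.

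The cost is one paragraph in the protocol and the same text in any analysis plan or committee charter. Power at the final analysis is almost unchanged. The real downside is a smaller chance of stopping early for efficacy.

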## Data collection and management

### Plans for assessment and collection of outcomes {18a}

The assessment and collection of trial data will start at patient enrollment (D0) including vital signs, specific therapies (i.e., albumin, transfusions), vital organ support, blood, urine, and ascitic fluid tests, repeatedly up to D7.

The trial protocol includes the daily collection of an 8-h (480 min) urine volume, at blocked nocturnal interval from 23 to 07 h, for measurement of creatinine clearance, based on the following formula: creatinine clearance (mL/min) = (urinary creatinine [mg/mL] × urine volume [mL])/(serum creatinine [mg/mL] × urine collection time [480 min]) [34].

Daily blood analysis includes complete hemogram, coagulation, and biochemistry and arterial blood gas. Ascitic fluid will be collected with every new paracentesis and repeated every 48 h in the intervention group for screening of infectious complications.

Collected trial variables are mainly included in clinical severity scores APACHE II [35], SAPS II [36], CLIF-C ACLF [37], CLIF-SOFA, SOFA [38], RIFLE [30], KDIGO [29], ICA-AKI [13], MELD [39], and MELD-Na [40] and incorporate liver disease etiology, precipitant event for critical illness, urine output, serum creatinine, estimated and measured creatinine clearance, and number of days on RRT, Glasgow coma score and West-Haven scale, number of days under vasopressor support and dosage, PaO_2_/FiO_2_ ratio, positive end-expiratory pressure and number of days under mechanical ventilation, total bilirubin, coagulation international normalized ratio, platelet count, arterial blood lactate and prescribed albumin dosage. Intermediate effect variables IAP and APP will be measured throughout ICU stay to test the trial rationale.

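### An efficacy stop at 30 patients, with 0.05 the only level stated, leaves power for IAP modestly below the 80% that the protocol states for 44 patients

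*Protocol article*

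**What the plan says.** Protocol article, Interim analyses {21b}: "An interim analysis will be performed when the trial completes the follow-up of 30 patients to assess for safety and outcomes". It continues: "The trial will be terminated in case of significant harm or if significant statistical difference on the primary outcome is achieved". The primary outcome is serum creatinine. The section gives no separate interim level and sets no condition on IAP, survival or the amount of safety data.

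Statistical methods {20a}: "A level of significance *α*= 0.05 will be considered". Sidedness is not given there. The sample size section works "with a one-sided alpha level of 0.05".

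Sample size {14} has two calculations. For IAP it takes "an expected clinically significant IAP decrease of 3 mmHg in the intervention group", with group values "13.7 ± 3.9 and 16.7 ± 3.9 mmHg, respectively", and concludes that "a total of 44 patients are considered necessary to detect a statistically significant difference, with 1:1 allocation ratio, 80% statistical power". For creatinine it takes a difference of 0.4 mg/dL with SDs of 0.45 and 0.48, and reaches 60 patients for 95% power. The total is set at 70 to allow for about 15% attrition or non-adherence.

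Plans for assessment and collection of outcomes {18a} gives IAP its role: "Intermediate effect variables IAP and APP will be measured throughout ICU stay to test the trial rationale".

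**The concern.** The sample size section treats 44 patients as the minimum for a properly powered test of IAP. The interim section ends the whole trial at 30 if creatinine alone is significant. No section reconciles the two. A significance test at 0.05 is an easy hurdle at 30 patients if the assumed creatinine effect is true, because the trial is sized for 95% power on that outcome.

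The protocol assumes that renal function depends on IAP. An early creatinine result with too little IAP data would leave that explanation weakly tested. Estimates from trials stopped on significance also tend to overstate the effect.

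**Working it through.** **Inputs.** IAP: difference 3 mmHg, SD 3.9. Creatinine: difference 0.4 mg/dL, SDs 0.45 and 0.48. Level 0.05, interim at 30 (15 per arm), final size 60 (evaluable) to 70 (planned). All are from the Protocol article. The within-arm correlation between creatinine and IAP is not given, so 0 to 0.6 is assumed.

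**Formula.** For n per arm, λ = δ / (σ·√(2/n)), and one-sided power = 1 − F(t(0.95; 2n−2); 2n−2, λ), where F is the noncentral t distribution. Two-sided power uses the 0.975 quantile.

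**Step 1: reproduce the plan's figures.**
- IAP, n = 22: λ = 3 / (3.9·√(2/22)) = 2.551, critical t = 1.682, one-sided power 80.6%. The stated 44 is reproduced.
- Creatinine: pooled SD = √((0.45² + 0.48²)/2) = 0.465. With n = 30, one-sided power is 95.0%. The stated 60 is reproduced.
- Attrition: 60/0.85 = 70.6 and 60 × 1.15 = 69, so 70 is reasonable.

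**Step 2: chance of stopping at 30.** λ = 0.4 / (0.465·√(2/15)) = 2.355. Against a critical t of 1.701 the one-sided chance is 74.3%. Against 2.048 the two-sided chance is 62.3%. Across SDs of 0.48 to 0.45 the ranges are 72-77% and 60-65%. With 26 evaluable patients they are 69% and 56%.

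**Step 3: IAP power by trial size.**

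| Patients | One-sided | Two-sided |
|---|---|---|
| 30 | 65.9% | 53.0% |
| 44 | 80.6% | 70.3% |
| 60 | 90.3% | 83.4% |
| 70 | 93.8% | 88.7% |

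**Step 4: overall IAP power with the rule, one-sided.** At zero correlation this is the stop chance times power at 30, plus the rest times power at the final size:
- final size 70: 0.743 × 0.659 + 0.257 × 0.938 = 0.731
- final size 60: 0.743 × 0.659 + 0.257 × 0.903 = 0.722

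Simulation of the two-stage design with correlation up to 0.6 raises these to about 77% (final 60) and 79% (final 70). The range is therefore about 72-79%, against 90-94% without the rule.

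**Step 5: expected size.** Final 70: 30 + 40 × 0.257 = 40.3 one-sided, and 30 + 40 × 0.377 = 45.1 two-sided. Final 60: 30 + 30 × 0.257 = 37.7 and 30 + 30 × 0.377 = 41.3. The range is about 38-45 patients.

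**Step 6: estimate at a stop.** In simulation the mean creatinine difference among stopped trials is 0.47 mg/dL (one-sided) and 0.50 (two-sided), with a true value of 0.40.

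**Step 7: sensitivity to the creatinine SD.** Outcomes {12} assigns 4 mg/dL after renal replacement therapy or death. Suppose 10% of each arm receive that value (assumed) and the rest follow the stated means and SDs. The intervention-arm mean is 0.1 × 4 + 0.9 × 0.9 = 1.21. Its variance is 0.1 × 16 + 0.9 × (0.45² + 0.9²) − 1.21² = 1.047, so the SD is about 1.0. Keeping the 0.4 difference, the stop chance is 28% one-sided and 19% two-sided at SD 1.0, and 55% and 42% at SD 0.6.

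**Step 8: a strict boundary.** At a nominal 0.003 for the look, the stop chance is 29% one-sided. At zero correlation and final size 70, one-sided IAP power is 0.291 × 0.659 + 0.709 × 0.938 = 0.857. Simulation to correlation 0.6 takes it to about 91%. Two-sided, the range is about 81-86%.

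**The case against.** The arithmetic is not in dispute. The dispute is over how much follows from it, and several stronger readings should be set aside.

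- *The trial will probably end at 30 if the intervention works.* This holds only on the stated SDs. They come from an external cohort, and nothing shows that they include the 4 mg/dL assignment. The trial also has strata for creatinine of 1.5 mg/dL or more. Step 7 shows how quickly the stop chance can fall below one half.
- *IAP power drops from 80% to 53%.* This sets a two-sided figure, conditional on stopping, against a one-sided target. Two-sided, 44 patients give only 70% with no stop at all. Like for like, the overall loss is about 1 to 8 points and is smallest at high correlation, the direction in which the protocol's own causal assumption points.
- *The problem is separate from the interim significance level.* A Pocock-type nominal 0.029 (two-sided) would still stop 53% of trials, which makes this tempting. But Step 8 shows that a strict boundary restores at least 80% with the efficacy stop kept. The harm comes largely from looking at 0.05.
- *The stop is what leaves survival and complications underpowered.* The Discussion already concedes low power for some secondary outcomes and for complications at 70. The stop makes this worse. With no events in an arm, the one-sided 95% upper limit is 1 − 0.05^(1/15) = 18% with 15 patients, against 8% with 35. It is not the cause.

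It is also fair to say that the final size is set by creatinine, that IAP is a secondary outcome, and that an independent monitoring committee with a statistician exists. An analysis plan not shown may set a stricter boundary. What stands is that this document orders termination on significance, gives 0.05 as its only level, and states a power for IAP that the design with that rule does not have.

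**Conclusion.** The point holds in a limited form. Read at 0.05, the rule stops about 74% of trials at 30 one-sided (62% two-sided) on the protocol's own creatinine inputs. A trial stopped there has 66% one-sided power for IAP. Overall one-sided IAP power is about 72-79%, modestly below the stated 80%, and the creatinine effect reported at a stop is overstated by about 0.07-0.10 mg/dL on average.

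These results rest on the stated differences and SDs, on 0.05 applying at the look, on a final size of 60 to 70, and on an assumed correlation of 0 to 0.6. A wider creatinine SD lowers the stop chance. The documents do not support the view that efficacy stopping is wrong in itself here, nor that this is a defect independent of the interim level. Two looks at 0.05 also raise the type I error to about 8.0-8.5%. Both points concern the same sentence and should be handled together.

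**What to change.** In Interim analyses {21b}, keep the look at 30 for safety with its harm stop. Then either:

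- allow an efficacy stop only at a strict boundary stated in advance, for example of O'Brien-Fleming type with a nominal level of about 0.003. This stops about 29% of trials one-sided and, with 70 patients, keeps IAP power at about 86-91% one-sided or 81-86% two-sided; or
- drop the efficacy stop and test the primary outcome once, at the end.

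If the 0.05 stop is kept, Sample size {14} should state one-sided IAP power of about 72-79% and an expected size of about 38-45 patients under the assumed effect.

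The change is one or two sentences and adds no patients beyond the planned 70. The cost is that a truly effective treatment is less often declared early. Up to 40 more of the planned patients are then randomised, half of them to the control arm.

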### Methods for additional analyses (e.g., subgroup analyses) {20b}

Subgroup analyses are planned to compare the outcomes of groups of patients with or without serum maximum creatinine ≥ 1.5 mg/dL, maximum or mean IAP value ≥ 16 mmHg before randomization, and baseline or mean APP value < 60 mmHg up to D7.

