## Assignment of interventions: allocation

### Sequence generation {16a}

The patient allocation method consists of stratified randomization with blocks within each subgroup. This method is particularly useful with randomizing small samples due to the ability to create balanced groups regarding predetermined variables or characteristics at the beginning of the trial, reducing differences in baseline trial groups characteristics’ that could harm later result analysis and conclusions.

In this small sample size trial, patients will be stratified according to maximum serum creatinine and maximum IAP, expected to be the two most important variables to balance between trial groups at baseline. Stratified randomization will homogenize trial groups ad initio to reduce the probability of unbalanced baseline group characteristics and biased results.

The stratification process will use two strata, namely, maximum IAP and maximum serum creatinine, thus creating four subgroups (I–IV): (I) IAP < 16 mmHg + serum creatinine < 1.5 mg/dL, (II) IAP < 16 mmHg + serum creatinine ≥ 1.5 mg/dL, (III) IAP ≥ 16 mmHg + serum creatinine < 1.5 mg/dL, and (IV) IAP ≥ 16 mmHg + serum creatinine ≥ 1.5 mg/dL [4, 13]. Each subgroup (I–IV) contains sequential blocks of randomized trial group allocation (A) control and (B) intervention, with a 1:1 ratio (i.e., *AABB*, *ABAB*, *BABA*, *BBAA*), as exemplified in Table 1.

**Table 1 Tab1:** Stratification subgroups (I-IV) created using maximum intra-abdominal pressure (IAP) and serum creatinine as strata. Example of stratified randomization with blocks within each subgroup (A, B)

Stratification subgroups (I–IV)	Creatinine < 1.5 mg/dL	Creatinine ≥ 1.5 mg/dL
IAP < 16 mmHg	I) ABAB, ABBA,…	III) BABA, BBAA,…
IAP ≥ 16 mmHg	II) BABA, AABB,…	IV) BBAA, BAAB,…

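### The subgroup sentence compares patients with and without a feature, which measures prognosis and cannot show whether the CPP-versus-LVP effect differs between subgroups

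*Protocol article*

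**What the plan says.** The Protocol article, Methods for additional analyses {20b}, consists of one sentence. It opens "Subgroup analyses are planned to compare the outcomes of groups of patients with or without serum maximum creatinine" (cut-off 1.5 mg/dL) and goes on to "maximum or mean IAP value ≥ 16 mmHg before randomization, and baseline or mean APP value < 60 mmHg up to D7". That makes three factors and five definitions: maximum creatinine, maximum IAP, mean IAP, baseline APP and mean APP up to D7. Neither CPP nor LVP is mentioned.

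The creatinine and IAP cut-offs are those used for stratified randomisation in Sequence generation {16a}, "thus creating four subgroups (I–IV").

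Statistical methods {20a} gives the tests between arms ("test will be used to compare study groups, assuming a non-normal distribution", or a t-test) and adds that "For all regression studies, univariable and multivariable analyses will be performed to account for potential confounders". On the level it says only "A level of significance *α*= 0.05 will be considered", whereas Sample size {14} works "with a one-sided alpha level of 0.05". Nothing in the article turns the with-versus-without contrast into a comparison of treatment effects.

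**The concern.** A subgroup analysis in a randomised trial is normally read as an answer to whether the treatment effect differs between kinds of patient. The stated comparison cannot answer that. Patients who enter with high creatinine can be expected to have higher creatinine at day 7 in either arm. A with-versus-without comparison will show that difference whether CPP helps everyone, helps some or helps no one. The comparison is also not protected by randomisation.

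The sentence may be loose wording for CPP versus LVP within each subgroup. The natural misuse is then to set a significant p-value in one subgroup against a non-significant one in the other. At this sample size, that pattern arises often by chance when the effect is the same in both.

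One listed factor has a separate problem. Mean APP up to D7 is measured after randomisation, and the protocol expects drainage to change APP. Groups defined by it are partly a result of treatment.

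At stake is the reading of the subgroup results. The primary comparison between arms is not affected.

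**Working it through.** **Inputs.** From Sample size {14}: creatinine difference 0.4 mg/dL; SDs 0.45 and 0.48; one-sided alpha 0.05; 95% power; 60 patients, set at 70. The share of patients with each feature is not given. An even split is assumed first, then varied.

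**Step 1: reproduce the plan's own figure.** SD = √((0.45² + 0.48²)/2) = 0.465. By the noncentral t with 30 per arm, one-sided 0.05, power is 0.950, so 60 patients, as stated. The inputs are therefore read correctly.

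**Step 2: the contrast as written.** Take 70 patients, 35 with and 35 without the feature, and assume that the feature shifts creatinine by 0.4 mg/dL. Two-sided t-test at 0.05:
- CPP has no effect: SD 0.465, power 94% (95% in 8,000 simulated trials).
- CPP lowers creatinine by 0.4 equally in both groups: the SD pooled over arms is √(0.465² + 0.2²) = 0.506, power 90% (91% simulated).

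The result is almost the same whether CPP works or not. It reflects the prognostic shift and carries no information on effect modification.

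**Step 3: separate arm comparisons in two equal halves.** About 70/4, or 17 per arm per half. SE = 0.465 × √(2/17) = 0.160; noncentrality 0.4/0.160 = 2.51; 32 degrees of freedom.
- Power p = 0.79 one-sided, 0.68 two-sided.
- Chance that exactly one half is significant under an identical true effect, 2p(1 − p): 2 × 0.79 × 0.21 = 0.33 one-sided; 2 × 0.68 × 0.32 = 0.43 two-sided. (With 17.5 per arm: 0.32 and 0.42.)
- With no effect at all: 2 × 0.05 × 0.95 = 0.095.
- Uneven splits with 70 patients, common effect, pA(1 − pB) + pB(1 − pA): at 70/30, 42% one-sided and 52% two-sided; at 80/20, 54% and 64%.

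**Step 4: the interaction instead.** With 17.5 per cell, SE = 0.465 × √(4/17.5) = 0.222, twice the main-effect SE of 0.465 × √(2/35) = 0.111. For a 0.4 mg/dL difference in effect, noncentrality is 0.4/0.222 = 1.80 on 66 degrees of freedom.
- Two-sided power is 43% at 50/50, 37% at 70/30 and 29% at 80/20.
- The difference detectable with 80% power is (1.997 + 0.842) × 0.222 = 0.63 mg/dL at 50/50, rising to 0.79 at 80/20. Both exceed the planned main effect.
- The simulated false-positive rate was 4.8% to 5.3% whatever the feature's prognostic strength.

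**Step 5: sensitivity to the assigned value.** Outcomes {12} assigns 4 mg/dL after renal replacement therapy or death, which widens the SD. If 20% of patients were assigned it (assumption) and the rest averaged 1.1 mg/dL (midway between 0.9 and 1.3), SD = √(0.8 × 0.465² + 0.2 × 0.8 × 2.9²) = 1.23. Power within a half falls to about 24% one-sided or 15% two-sided, and exactly one half is significant in about 36% or 25% of trials. Interaction power falls below 43% too.

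**The case against.** Four points can fairly be made for the plan.

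- **The model may be in an analysis plan.** This is a condensed article, and the way subgroup effects are estimated and tested is commonly left to a SAP, which is not shown. That stands: the absence of an interaction term is not in itself a fault. The point rests instead on the contrast that the sentence does state.
- **The literal contrast has a use.** Objectives {7} gives as general aim to assess the impact of intra-abdominal hypertension on organ dysfunction and outcomes. Comparing patients with and without high IAP or low APP serves that aim descriptively. This stands in part. It justifies keeping such a comparison under its own label, but does not make it an analysis of treatment effect.
- **No misuse is announced.** A reader might infer that the plan will often produce a subgroup difference that is not there. The article does not say that subgroup claims will be drawn from separate p-values. The 33% to 43% applies only if CPP has a real common effect and p-values are contrasted; with no effect the figure is about 10%. On the literal reading, the difference shown is a real one in prognosis.
- **The weight of the analysis can be overstated.** A reader might also infer that the prevention-versus-treatment question rests on the IAP subgroup. The documents do not say so. They name prevention and treatment together, the Trial hypothesis speaks only of treatment, and subgroups are filed under additional analyses.

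**Conclusion.** The point holds in a limited form. Followed as written, the subgroup sentence gives a non-randomised prognostic comparison that cannot show whether the CPP effect differs, and nothing else in the article corrects it. If within-subgroup arm comparisons are meant, setting their p-values side by side would show exactly one significant half in about a third (one-sided) to 43% (two-sided) of trials under an identical 0.4 mg/dL effect. Those figures rest on the plan's SD, an assumed even split and about 70 patients with outcome data. An uneven split raises them; the wider SD in Step 5 lowers them. They describe a risk of misreading, not a stated intention.

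Even the correct analysis has at most about 43% power for a 0.4 mg/dL interaction, so it can only be exploratory. The mean APP up to D7 factor is a separate defect that an interaction term would not repair. The sentence should be corrected; the primary analysis does not depend on it.

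**What to change.** Reword the sentence in Methods for additional analyses {20b} along these lines:

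- For each factor measured before randomisation (creatinine, IAP, baseline APP), one model of the primary outcome will contain arm, factor and arm × factor.
- The CPP-minus-LVP effect will be reported with its 95% CI at each level of the factor, together with the interaction estimate and its 95% CI.
- The analyses are exploratory, and no subgroup claim will be drawn from p-values within levels.
- Mean APP up to D7 is removed as a subgroup factor, or reported as descriptive only, because it is measured after randomisation and treatment can change it.
- Any with-versus-without comparison kept for the general aim is labelled prognostic and non-randomised.

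The cost is a few lines of text. No new data are needed and the sample size does not change. The downside is that subgroup statements become more cautious.
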